#### *Vascular and autonomic testing*

Upon completion of the venipuncture procedure, a standardized snack was consumed. Participants were instrumented for collection of continuous R-R intervals with a lead II electrocardiogram (Colin Pilot 9200, Colin Medical Instruments, San Antonio, Texas) and respiratory rate by belt transducer (Pneumotrace II, ADInstruments, Colorado Springs, Colorado) secured around the thorax. Data were collected during ten minutes of supine rest, with external stimuli such as light and noise controlled to ensure signal stability. All measures were sampled at 1000 Hz, input into a data acquisition board (PowerLab ML795, ADInstruments) for analog-to-digital signal conversion with LabChart7Pro software (ADInstruments) and stored for offline analysis.

The left carotid and brachial arteries were imaged longitudinally just proximal to the carotid sinus and anticubital fossa, respectively, using B mode ultrasound (VingMed System 5, GE Ultrasound A/S, Horton, Norway). The average of three measures of each systolic and diastolic diameter and intima media thickness were recorded for each site. A sphygmomanometer blood pressure cuff was then secured on the left forearm just distal to the elbow for assessment of flow mediated dilation [26]. The brachial artery was imaged as described above. The cuff was inflated to 200 mmHg for five minutes and then deflated to induce reactive hyperemia. Beat-by-beat flow and continuous brachial arterial diameter were recorded with Doppler ultrasound for five minutes following the release of the pressure cuff.

#### *Fitness assessment and exercise prescription*

The Step Test and Exercise Prescription (STEP™) protocol was used for fitness assessment and exercise prescription. This tool is endorsed by the College of Family Physicians of Canada as part of accredited Continuing Health Education curriculum for improving physical activity education among family physicians. It has been validated in adults aged 18-65 years, (Unpublished observations) and 65-85 years [27]. In adults aged 18-65 years, the fitness assessment was shown to overestimate fitness by 7 ml/kg/min [Unpublished observations]. However, since STEP™ results (i.e. aerobic fitness) are used as a motivational tool, its use has been recommended for counselling and prescription purposes, but not as a primary outcome measure [Unpublished observations]. STEP™ has proved useful as a tool in primary care to increase physical activity and improve metabolic syndrome and global cardiometabolic risk factors [28].

The STEP™ test was conducted by a research assistant with training in kinesiology. Resting heart rate was measured by palpation of the radial artery for 10 seconds. Participants were instructed to step up and down a set of two steps (each with a 20 cm rise) twenty times at a pace considered normal for climbing stairs (Figure 1). Upon completion of the test, post-exercise heart rate was palpated from the radial artery for a 10-second count. Time to complete the test (in seconds) and post-exercise heart rate (in beats per minute; bpm) were entered into an equation to estimate fitness (maximal oxygen uptake) [28]. Fitness was classified as poor, fair, good or excellent based on age, sex and maximal oxygen uptake (Additional file 1).

**Figure 1 F1:**
[figure not shown]
Step Test and Exercise Prescription (STEP™) protocol.

The same research assistant who conducted the STEP™ test counselled the participant and prepared an individualized exercise prescription based on fitness and participant preferences. Participants worked with the research assistant to identify three personal fitness goals. Additionally, barriers to exercise or lifestyle changes were identified and strategies to overcome these barriers were developed. The final exercise prescription was based on American College of Sports Medicine guidelines [29] and included the frequency, intensity, type and duration of exercise. Frequency was ideally set at (or increased to) most days of the week. Training heart rate was calculated as a percentage of the age predicted maximum heart rate (220-age) and was based on fitness classification from the STEP™ fitness assessment with 70, 75, 80 and 85% of predicted maximum heart rate prescribed for participants with poor, fair, good and excellent fitness, respectively. The type of exercise most commonly prescribed was walking, but other aerobic activities were also chosen including, but not limited to, aerobic exercise classes, swimming, cycling and team sports. Resistance exercises were also prescribed one to three days per week, depending on fitness, and consisted of exercises such as squats, calf raises and push ups. When participants had equipment available to them for resistance exercise, programs were designed specific to their needs. All participants were encouraged to accumulate a minimum of 150 minutes per week of moderate-to-vigorous intensity physical activity according to global guidelines [30]. Exercise bouts could be a minimum of 10 minutes with the goal of increasing time to 30 minutes per session or more. Since participants in the intervention group received a pedometer, step goals were also included in their prescription [31].

Participants in the active control group were given a journal to log their activity daily including exercise heart rate. The intervention group logged their activity with their mobile health monitoring application (see below).

### Behavioural and health status questionnaires

Participants completed the Short Form-36 questionnaire [32]. Raw scores were transformed using the guidelines developed by Medical Outcomes Trust. Eight dimensions of quality of life were examined: physical functioning; role-physical; role-emotional; bodily pain; vitality; mental health; social functioning; and general health. Raw scores were converted to a score out of 100 for each dimension, with 0 and 100 representing an extremely poor and extremely good quality of life, respectively. The SF-36 has proved to be valid and reliable [33,34]. Dietary habits, exercise, blood glucose testing, foot care and smoking habits were recorded using the Summary of Diabetes Self-Care Activities survey, which is a brief, reliable and valid measure of these lifestyle behaviours [35].

The Decisional Balance scale was used to assess perceptions of pros and cons to participating in exercise [36] and the Exercise Self-efficacy scale was used to assess confidence in participating in an exercise program [37].

A survey assessing current technology use, comfort with and burden of technology was administered at each visit to the intervention group. The active control group also completed a survey at V3. This survey was included solely to receive feedback regarding the technology, which would be used to modify the protocol for future studies.

### Mobile health technology

In addition to the exercise prescription, the intervention group also received a mobile health technology kit for self-monitoring of biometrics and physical activity. We previously tested the feasibility of delivering this intervention to this population and showed that the technology was accepted and motivational to participants in the pilot study [21]. The kit included a smartphone (Blackberry® Curve 8300 or 8530) equipped with Healthanywhere health monitoring application (Biosign Technologies Inc., Markham, Ontario, Canada), a Bluetooth™ enabled blood pressure monitor (A & D Medical, UA-767PBT, San Jose, California, USA), a glucometer (Lifescan One Touch Ultra2™, Milpitas, California, USA) with Bluetooth™ adapter (Polymap Wireless, PWR-08-03, Tucson, Arizona, USA) and a pedometer (Omron, HJ-150, Kyoto, Japan). All participants were required to attend a group training session (approximately two-hour duration) following V0. Those who could not attend group training sessions were given an individual training session at the end of their baseline visit. During the training session, participants were instructed on proper use of devices and techniques to ensure proper measurements. Participants were given the opportunity to practice taking measurements, to ask any questions related to the mobile health protocol and were provided with a telephone number and email address of study personnel for troubleshooting.

Throughout the intervention period, home blood pressure and fasting plasma glucose were to be submitted thrice weekly upon waking. Blood pressure was to be taken in the seated position with feet flat on the floor, back supported and arm supported at heart height. Blood pressure was measured once following five minutes of seated rest. Fasting plasma glucose was measured prior to consumption of food or drink. The pedometer was to be attached to the waistband at the front of the hip daily upon waking and removed just before bed (or during activities that could damage the pedometer, such as swimming and contact sports). Pedometer steps were input nightly. Home body weight was measured monthly with consistent timing and equipment. All submitted measures were date and time stamped and transmitted in real time to a secure database that was monitored by research personnel. Thresholds were set for systolic blood pressure (60-220 mmHg), diastolic blood pressure (40-110 mmHg) and fasting plasma glucose (3.0-15.0 mmol/L). Submitted readings that were outside these limits triggered an alarm that was sent to the study physician’s smartphone for immediate follow-up. Trends for consistently increasing measures were monitored by research assistants and brought to the study physician’s attention as necessary for follow-up.

Exercise was logged with the Healthanywhere activity tracking module. An individualized list of activities and target heart rate from the participant’s exercise prescription was compiled, and the participant was to select the completed activity and heart rate achieved following each planned exercise session.

Participants received a heart rate monitor (Suunto Memory Belt, Vantaa, Finland), which was secured around the chest on three occasions during the week following each visit. On the least active day of the week, participants were to wear the monitor for a 24-hour period and on two separate occasions they were to perform an orthostatic challenge with five minutes each of supine rest, seated rest and quiet standing. Heart rate monitors were returned to the clinic and data were downloaded to a personal computer with Suunto Training Manager software (Version 2.3.0).

Details of security for data transfer and database storage has been reported elsewhere [21]. Briefly, real-time data were encrypted and transmitted from the smartphone to the server and database by secure internet protocol. Biometric data were deidentified for transmission and linked to participant data once on the protected server. Database access was limited to authorized researchers. Healthanywhere accounts were controlled and protected remotely so that in the case of device loss, the account could be deactivated to prevent unauthorized access to participant health information.

### Data processing

#### *Mobile health*

Deidentified health data will be downloaded from the Healthanywhere database for offline analysis. Compliance to the self-monitoring protocol will be calculated as the percentage of measurements that were completed overall and for each device. The average of monthly measurements will be calculated and used to examine change in mobile health biometric and physical activity measures over time. Data from mobile health exercise logs will be processed the same as paper logs, described below.

#### *Exercise log data*

Entries from exercise logs will be input to a personal computer and coded according to exercise type. Exercise data will be used for descriptive purposes only and exercise characteristics such as frequency, duration and intensity were documented. Compliance to the exercise prescription will be examined by calculating the percentage of exercise sessions completed.

#### *Heart rate variability processing*

Data files from electrocardiogram collection of R-R interval in the clinic in all participants and home monitoring of R-R interval for 24 hours and during an orthostatic challenge will be converted to text files for analysis with heart rate variability software (Hearts v7, Heart Signal Co., Oulu, Finland). Editing of the R-R interval time series is to be performed by a single investigator. All electrocardiogram signals will be manually scanned for ectopic or non-sinus beats, which will be deleted from the time series. Ninety percent of data are needed for inclusion of short-term heart rate variability recordings and 80% of data are needed for inclusion of long-term 24-hour recordings. Time domain heart rate variability analyses include heart rate, standard deviation of normal-to-normal intervals the root square mean of successive differences. The heart rate variability spectrum will be computed with the non-parametric fast Fourier transform method. Ultra low (0.0-0.003 Hz) and very low frequency powers (0.003-0.04) will be examined for 24-hour data and low (0.04-0.15 Hz) and high frequency powers (0.15-0.4 Hz) and the low-to-high frequency power ratio will be examined for both 24-hour and short-term data. A Poincaré plot will be formed by plotting each R-R interval against the following one to create a scatter plot. The standard deviation of the width and length will be calculated. The detrended fluctuation analysis method will be used to examine fractal characteristics of heart rate fluctuations. The root-mean square fluctuations of integrated and detrended data will be measured in observation windows and then plotted against the size of the window on a log-log scale. α_1_ will be calculated from the slope of the line (from 4-11 beats). Approximate entropy quantifies the regularity of time series data by calculating the likelihood that runs of patterns that are close will remain close on the next incremental comparison. A greater value represents greater unpredictability in a system. Approximate entropy will be calculated from 500 beats and will be computed with length, m = 2 and tolerance, r = 20%.

#### *Vascular data processing*

Systolic and diastolic radiuses along with pulse pressure will be entered into equations to calculate arterial compliance and distensibility [38]. Flow mediated dilation will be calculated as the maximal percentage increase in vessel diameter above baseline and percent change, absolute change and baseline diameter will be reported [39].

### Statistical analysis

#### *Outcome measures*

Clinic systolic blood pressure was chosen as the primary outcome measure.

Secondary outcomes included other metabolic syndrome, clinical and novel cardiometabolic risk factors. Scores from behavioural and health status questionnaires were also included in secondary outcomes.

Tertiary outcomes were mobile health variables including biometrics, activity and compliance to the monitoring protocol.

#### *Sample size calculation*

The sample size was based on differences in mean change between the intervention and active control groups in systolic blood pressure (primary outcome measure) at 12-weeks. The sample size calculation assumed 80% power and two-sided significance level of 0.05. We estimated that the smallest difference between groups in mean change that would be expected was 6 mmHg and we assumed a common standard deviation of 12 mmHg. Therefore, it was determined that 63 participants would be required per group. By assuming a 15% drop-out rate, this would increase our required sample size to 73 participants per group. Since we are using an Analysis of Covariance (ANCOVA) to perform data analysis (primary analysis), this sample size estimation may be considered conservative.

Data will be analysed following the Intent-to-Treat approach. Analyses will include all safety evaluable patients who have both baseline and valid post-baseline data. In instances where a participant may not have completed the final visit of the protocol but was subjected to the above procedures before study termination, a last observation carried forward approach will be used for analysis. Baseline data will not be carried forward.

For all continuous outcome variables, distributions will be examined to assess normality and presence of outliers; transformations will be undertaken as appropriate. For categorical outcome variables, frequency tables will be examined to ensure there are no out-of-range values.

Descriptive statistics will be computed for baseline demographic characteristics and for all outcome measures, at each time point. Specifically, means and standard deviations will be calculated for continuous variables and frequency counts and percentages will be calculated for categorical variables.

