## Methods/Design

### Study design

This study was a randomized controlled trial with two intervention arms: 1) the intervention group, which received a tailored exercise prescription and a mobile health technology kit; and 2) the active control group, which received only a tailored exercise prescription. Adults aged 18-70 years were screened for inclusion. Participants (*n* = 149) presenting with at least two metabolic syndrome risk factors reported to the clinic (Gateway Rural Health Research Centre, Seaforth, Ontario, Canada) at baseline (V0) and for 12- (V1), 24- (V2) and 52-week (V3) follow-up visits.

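### The 73 per group stated for 15% drop-out leaves about 62, not the required 63; dividing by 0.85 gives 75 (74 from the unrounded requirement)

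*Protocol article*

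**What the plan says.** The section on sample size calculation in the protocol article bases the size on the 12-week comparison: "The sample size was based on differences in mean change between the intervention and active control groups in systolic blood pressure". On error rates it says: "The sample size calculation assumed 80% power and two-sided significance level of 0.05". The target is the "smallest difference between groups in mean change that would be expected was 6 mmHg", and for variability "we assumed a common standard deviation of 12 mmHg". The result before drop-out is: "Therefore, it was determined that 63 participants would be required per group". The next step is: "By assuming a 15% drop-out rate, this would increase our required sample size to 73 participants per group". No inflation formula is shown, and no period is attached to the 15%.

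The section then remarks that the estimate may be conservative because the primary analysis is an ANCOVA. It also limits the analysis to participants with baseline and valid post-baseline data, and rules out carrying baseline values forward. The study design section gives the number taking part, "Participants (*n* = 149) presenting with at least two metabolic syndrome risk factors", and places the first follow-up visit at 12 weeks.

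**The concern.** An allowance for drop-out should leave the required number after the assumed loss. To keep n after losing a fraction d, one enrols n/(1 − d). Multiplying by (1 + d) always gives too few, because the loss applies to the larger enrolled number and not to n.

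Here 73 looks like the product of such a multiplication. A reader who checks 73 against 63 and 15% finds that the figures do not agree. At stake is whether the stated requirement can be trusted as it stands, and whether a later trial that reuses the calculation would repeat the slip, which grows with the assumed drop-out. At 15% the effect is small.

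**Working it through.** **Inputs**, all from the sample size section: difference 6 mmHg, SD 12 mmHg, two-sided alpha 0.05, power 80%, drop-out 15%. The enrolled total of 149 is from the study design section.

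**1. Reproduce the 63.**
n per group = 2 × (1.96 + 0.8416)² × (12/6)² = 62.79, rounded up to 63. This matches, so the article evidently used the normal approximation. A t-test basis gives 63.77, hence 64.

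**2. Look for the route to 73.**
- 63 × 1.15 = 72.45, rounded up to 73: matches.
- 63/0.85 = 74.12, rounded up to 75: does not match.
- 62.79/0.85 = 73.87: gives 73 only by truncation, whereas 62.79 was rounded up to 63. Rounded up, it gives 74.

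Multiplication by 1.15 is therefore the likeliest route, but it is an inference.

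**3. Check 73 against its purpose.**
- 73 × 0.85 = 62.05 remaining, below both 63 and the unrounded 62.79.
- Largest loss at which 73 still keeps 63: 1 − 63/73 = 13.7%.

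**4. Corrected inflation.**
- From the rounded 63: 75 per group, 150 in total; 75 × 0.85 = 63.75 remain.
- From the unrounded 62.79: 74 per group, 148 in total; 74 × 0.85 = 62.9 remain.
- Stated: 73 per group, 146 in total. The gap is 1 to 2 per group, or 2 to 4 in total.

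**5. Effect on power, unadjusted comparison.**
Power = Φ(√(n/2) × 6/12 − 1.96).
- n = 62: Φ(2.784 − 1.96) = 79.5%.
- n = 63: Φ(2.806 − 1.96) = 80.1%.

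The loss is about 0.6 percentage points.

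**6. Effect under the planned ANCOVA.**
Adjusting for baseline multiplies the required n by about (1 − r²), where r is the correlation between baseline and change. For 62.05 to suffice, 62.79 × (1 − r²) ≤ 62.05, so r² ≥ 0.0118 and |r| ≥ about 0.11. The article gives no correlation. As an illustration, assume that 12 mmHg is the SD of change and that the variances at baseline and 12 weeks are equal. The residual SD is then 12 × √((1 + ρ)/2), with ρ the correlation between the two measurements. For assumed ρ of 0.3, 0.5 and 0.7, power at 62.05 per group is about 93%, 90% and 86%.

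**7. Actual enrolment.**
149 × 0.85 = 126.65, or about 63.3 per group if evenly split. The article does not give the group sizes.

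**The case against.** The strongest reply is that nothing turns on this. The planned analysis is an ANCOVA, which the article itself says makes the size conservative, and a baseline–change correlation of about 0.11 is enough to recover 80% power. Recruitment is reported as done, and 149 exceeds the 148 obtained from the unrounded requirement. All of this stands, and it rules out the stronger reading that a reader might infer, namely that the trial misses its stated power. The 79.5% belongs to an unadjusted comparison, which is not the planned one. But ANCOVA bears on power at a given number of completers; it does not make 73 the number that keeps 63 after 15% loss.

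Two further reservations also stand. The multiplication by 1.15 is not stated in the article. And the period of the 15% is not given: follow-up runs to 52 weeks, and someone who leaves after the 12-week visit still contributes to the primary comparison. The figure of 62 remaining therefore assumes that the whole 15% is lost before that visit.

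It might also be said that last observation carried forward protects the number analysed. It does not do so for the 12-week outcome: the first post-baseline visit is the 12-week visit itself, and baseline values are not carried forward.

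Finally, 75 is the right figure only on the normal approximation that the article used. On a t-test basis the requirement is 64, and 64/0.85 = 75.3 gives 76. This is a reason to correct the inflation on the article's own basis and not to mix the two.

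**Conclusion.** The point holds as a small arithmetic error in the stated requirement. With 63 required and 15% lost before week 12, 73 per group is short by 1 to 2 per group, depending on whether the unrounded 62.79 or the rounded 63 is inflated. The cost is about 0.6 percentage points of power for an unadjusted comparison, and the ANCOVA would probably offset it. The documents do not show an underpowered trial. The actual enrolment of 149 mends the consequence, assuming a roughly even split, but not the sentence. The point does not affect the analysis, the conduct or the interpretation of the results.

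**What to change.** In the sample size section, replace 73 per group with 75 per group (150 in total), show the formula 63/(1 − 0.15) = 74.1 rounded up, and add that the 149 enrolled, if evenly split, leave about 63 per group after 15% loss. It would help to say in the same sentence that the 15% refers to loss before the 12-week visit, if that is what was meant. The cost is one corrected sentence, with no extra enrolment and no change to the analysis.

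### The 12-week primary analysis is labelled intent-to-treat, but by the plan's own rules it is an available-case analysis that omits everyone without a week-12 clinic reading

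*Protocol article*

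**What the plan says.** All references are to the Protocol article.

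- **Label.** The Sample size calculation section says: "Data will be analysed following the Intent-to-Treat approach".
- **Analysis set.** The next sentence reads: "Analyses will include all safety evaluable patients who have both baseline and valid post-baseline data".
- **Missing data.** The same paragraph carries the last observation forward for a participant who did not complete the protocol's final visit, and adds: "Baseline data will not be carried forward".
- **Outcome and time point.** The Outcome measures section states: "Clinic systolic blood pressure was chosen as the primary outcome measure". The sample size rests on the between-group difference in mean change "in systolic blood pressure (primary outcome measure) at 12-weeks", and the same section calls ANCOVA the primary analysis. The 12-week analyses section assigns baseline-adjusted ANCOVA to that time point.
- **Visits.** Under Study design, participants attend "at baseline (V0) and for 12- (V1), 24- (V2) and 52-week (V3) follow-up visits".
- **Later analysis.** The 52-week analyses section extends the work to all time points with linear mixed models.

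**The concern.** Intent-to-treat normally means that everyone allocated is analysed in the arm to which they were allocated. A set that requires post-baseline data depends on what participants did after allocation, so the two adjacent sentences do not describe the same population.

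The missing-data rule does not close the gap at the time point that matters most. It may help at V2 or V3, where an earlier post-baseline value can exist, but it cannot help at V1.

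At stake is what the headline estimate describes. Under the label, a reader would take it as the effect in all allocated participants. Under the stated rules, it is a comparison of those who attended the 12-week clinic visit. The two arms ask different things of participants: device training and regular self-monitoring in one, a daily paper journal in the other. Attendance could therefore differ by arm. The 52-week analyses section says interpretation will rest mainly on estimates and confidence intervals, so the population behind the estimate matters directly.

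**Working it through.** **1. Reproduce the plan's sample size.** Inputs from the Sample size calculation section: "The sample size calculation assumed 80% power and two-sided significance level of 0.05"; "the smallest difference between groups in mean change that would be expected was 6 mmHg"; common SD 12 mmHg; equal groups.

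n per group = 2 × (1.960 + 0.842)² × 12² / 6² = 2 × 7.85 × 4 = 62.8, rounded up to **63**. This matches.

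Dropout: 63 × 1.15 = 72.45, rounded up to **73**. This matches. (Dividing instead, 63 / 0.85 = 74.1, gives 75; the gap of two is not the issue here.)

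**2. What the sample size assumes about dropouts.** 73 × 0.85 = 62 completers per group, close to the 63 required. The calculation treats dropouts as adding nothing to the primary comparison, which fits an available-case analysis. Power with 62 per group is 79.5%, so power is not the problem.

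**3. Follow each type of participant into the 12-week ANCOVA.**

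| Attendance after V0 | Meets the analysis-set wording? | Value available at week 12? | In the 12-week ANCOVA? |
|---|---|---|---|
| V1 attended | Yes | Observed | Yes |
| V1 missed, V2 or V3 attended | Yes | None: the only earlier value is baseline, which may not be carried | No |
| No visit after V0 | No | None | No |

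Home readings cannot fill the gap. The outcome is the clinic measurement, and under Mobile health technology only the intervention group received monitors.

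**4. How many.** Taking the 15% planning figure as the proportion without a V1 value, 149 × 0.15 = 22.4, so about **22** are left out and about **127** are analysed (149 × 0.85 = 126.7).

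**5. Can a bias be computed?** Let m be the proportion missing V1 in an arm, and g the shortfall in blood-pressure reduction of its missing participants relative to its completers (subscripts: I intervention, C control). The completer comparison overstates the all-allocated benefit by m_I × g_I − m_C × g_C. The document gives no value of g and no arm-specific m, so the inputs below are assumptions:

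| m_I | m_C | g_I (mmHg) | g_C (mmHg) | Overstatement (mmHg) |
|---|---|---|---|---|
| 15% | 15% | 6 | 0 | 0.15 × 6 − 0 = 0.9 |
| 15% | 15% | 6 | 6 | 0.9 − 0.9 = 0 |
| 20% | 10% | 6 | 6 | 1.2 − 0.6 = 0.6 |
| 10% | 20% | 6 | 6 | 0.6 − 1.2 = −0.6 |

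The result can be positive, zero or negative, depending on inputs that the document does not supply.

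**The case against.** The strongest reply is that nothing is hidden. The sentence after the label says who is analysed, and another says baseline is not carried forward, so a careful reader can work out the population. That is fair, and it makes this a matter of label and definition rather than concealment. It does not make the label right.

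A second reply is that a repeated-measures model is already planned. This also stands in part: participants who miss V1 but return later meet the set wording and would enter the 52-week mixed model. That model is not the 12-week primary, however, and it falls under the same restriction to participants with post-baseline data.

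A third reply is that an article leaves sensitivity analyses and rules for isolated missed visits to the full plan. Their absence is accordingly not the point. The point is that the rules the article does state conflict with the label it gives them. The term safety evaluable is undefined here, but may be defined elsewhere, and nothing rests on it.

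A reader might infer more than this, in three ways that the document does not support:

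- **That the primary result is biased, and in favour of the mobile health arm.** The document gives no differential loss and no outcomes for dropouts. Controls also had a daily task, and the Background section reports that pilot participants did not find the technology too time-consuming, although that pilot had no control group.
- **That 22 is a ceiling.** It is the expectation at a planning assumption; actual loss could be lower or higher.
- **That a mixed model or imputation would by itself remove bias from dropout related to outcome.** Participants with only a V0 value would be predicted from completers in the same arm with similar baselines, so the estimate would stay close to the completer result.

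**Conclusion.** The point holds as one of population and label. On the stated rules, the primary 12-week ANCOVA is an available-case analysis and not intent-to-treat, and it drops participants who miss V1 even when they come back. At 15% dropout, about 22 of 149 would be left out.

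This rests on reading the 12-week ANCOVA as the primary analysis, which the Sample size calculation section supports, and on applying the 15% to week 12, the time point for which the sample size was set.

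It does not establish that the estimate is biased. Baseline-adjusted ANCOVA on available cases is unbiased if missingness depends only on arm and baseline value. Outside that condition, neither the size nor the direction of bias can be obtained from the document.

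**What to change.** 1. Define the primary set as all allocated participants with a V0 value, analysed in the arm to which they were allocated, and drop the requirement for post-baseline data.
2. Take the 12-week between-group contrast from the linear mixed model already planned in the 52-week analyses section. Use all observed visits without carrying any value forward, and enter visit as a category so that week 12 can be read off directly. Participants who return at V2 or V3 then contribute.
3. Add a sensitivity analysis for missing V1, either delta-adjusted or return-to-baseline, because the mixed model alone does not address dropout that depends on the outcome.
4. Keep the present 12-week ANCOVA as a secondary analysis labelled available-case.

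**Cost.** A change of wording, a contrast from a model already planned, and one further analysis on existing data. The sensitivity estimate may be slightly less favourable. For example, if the planned 6 mmHg held in completers, 15% were missing in each arm and those missing showed no between-group difference, the estimate would be 0.85 × 6 = 5.1 mmHg. Power at 74 per group would then be about 73% (SD kept at 12 mmHg). That is acceptable for a sensitivity analysis.
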